### Intervention for peer coaches and participants

During the intervention, peer coaches interact with the peer participant for six months, with the frequency of interactions based on whichever group the peer participant was randomly assigned to as previously described. It is also optional for the peer coach to accompany the participant to at least one clinic visit. Topics to be discussed include current and target clinical goals for HbA1C, cholesterol, blood pressure, self-care activities, managing stress, and the SMART objectives. Coach-peer interactions will be documented with the following information: date, type of encounter (phone, in-person), duration, and topics discussed. Coaches will attend a monthly meeting to reinforce diabetes knowledge and communication skills. This meeting will be an open discussion based on their experiences interfacing with participants. Zoom will be used for the monthly meetings. Peer participants will receive a link to a brief REDCap survey by email every two weeks. If internet access is limited, we will send a hardcopy to the participant with a self-addressed stamped envelope. This survey will assess the frequency and duration of calls, other interactions with their peer, and the specific content that was covered. These self-report assessments will be used to track the effectiveness of the intervention.

### Mid-intervention

At mid-intervention, we will again convene stakeholders for two additional meetings with three primary goals: (1) assess progress on RE-AIM dimensions; (2) select RE-AIM dimensions that require additional attention, if necessary; and (3) give context to understand the reasoning behind any differences that might exist between pre-implementation (i.e., anticipated) and midstream (i.e., unanticipated) adaptations. To achieve the first two goals, we will use an iterative approach to RE-AIM, wherein at the first meeting, team members will be reminded of RE-AIM dimensions selected at project start-up and then asked to confidentially rate the importance and progress of each RE-AIM dimension thus far on a 5-point Likert scale with options to provide qualitative explanatory feedback for each rating. At the second meeting, we will present de-identified results from the survey and then engage in subsequent brainstorming/goal setting to determine best approaches, including possible midcourse EBI adaptations, to improve data collection for RE-AIM dimensions deemed most in need of increased attention. To meet the third goal, we will use a PRISM-based survey [39] and the same interview guide used at project start-up to give context to determinants of midcourse progress (including any identified adaptations).

### Post-intervention

#### Peer coaches and participants

At the end of the intervention, the research coordinator will collect HbA1C via fingerstick and the validated questionnaire data described in data collection from peer coaches and peer participants. Peer participants will then provide HbA1C levels and validated questionnaires again at 3- and 6-months post intervention.

#### Stakeholders

Finally, immediately upon program conclusion, we will convene a final team meeting with stakeholders, as well as a sample of randomly selected peer health coaches from each of the four factorial conditions, to collect RE-AIM outcomes data and conduct summative interviews with the same PRISM survey and qualitative interview guide as used at project onset and midpoint. Additionally, we will ask stakeholders and selected peer health coaches to complete a psychometrically validated brief 12-item survey [40] on perceptions of feasibility, acceptability, and appropriateness of both the overall EBI and each of the selected strategies (i.e., each component in the 2x2 factorial design); we will also randomly select participants from each condition to complete the same survey and complete exit interviews to explore perceived and actual factors underscoring participant satisfaction with the EBI and its components.

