#### 2. Evaluate the pragmatic implementability of the adapted EBI

Guided by the Practical, Robust Implementation and Sustainability Model (PRISM), a framework that incorporates RE-AIM dimensions (i.e., reach, effectiveness, adoption, implementation, and maintenance). Interviews will be conducted at three timepoints: (1) at beginning of implementation, (2) at implementation midpoint, and (3) upon conclusion. We will collect both qualitative and quantitative data to assess PRISM domains and give context to both anticipated and unanticipated EBI adaptations. We will use an iterative approach to RE-AIM to collaboratively monitor RE-AIM dimensions, guide any needed mid-course adjustments, and evaluate implementation outcomes. Finally, feasibility, appropriateness, and acceptability of the EBI will be assessed via a validated 12-item questionnaire.

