### Peer participants

#### Sample size

From a statistical perspective, the goal of this pilot and feasibility study is to obtain precise estimates of outcome variability and preliminary effect sizes for each factor (peer support intervention, contact frequency) that can be used to power a large-scale clinical trial. Empirical work by Whitehead and colleagues [36] provides guidance on sample size requirements for pilot studies to accurately estimate the needed size of future trials. For a main trial that aims for 90% power with a two-sided α = .05, a pilot sample size per arm of 25 would be needed in anticipation of a small standardized effect size (e.g., Cohen’s f = 0.1). This study is interested not only in main effects, but also an interaction between peer support intervention and contact frequency. Given that interactions are notoriously underpowered [37]—and given anticipated participant attrition—the decision was made to recruit 19 participants per condition for a total sample size of 76. With this sample size, the detectable effect size for a between-group difference in the primary outcome is Cohen’s f = 0.33 at 80% power with a two-sided α = .05.

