**Secondary Outcomes**	
Refine proposed operationalizations of RE-AIM dimensions	Qualitative interviews
Assess RE-AIM dimensions	Qualitative interviews
RE-AIM outcomes	Qualitative interviews
PRISM survey and interview guide	A PRISM-based survey [40] and an interview guide tested in previous applications of PRISM [34] across health systems to analyze PRISM contextual determinants
Feasibility, acceptability, and appropriateness survey	A psychometrically validated brief 12-item survey [40]

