#### Assessing implementation

For all PRISM-guided interviews, two members of the research team with academic training and pragmatic experience in implementation science as well as substantial qualitative research experience will independently code the data and map responses to relevant PRISM domains, as outlined in previous applications of PRISM [34]. Should coding conflicts arise, a skilled implementation scientist with ample research using PRISM/RE-AIM will mediate and help build coding consensus. Data from midpoint iterative RE-AIM planning will be used primarily as quality improvement and will be presented to members of the implementation and research teams using descriptive statistics, graphs, charts, and de-identified thematic analysis of any explanatory feedback. Finally, for the 12-item feasibility, acceptability and appropriateness survey, scores for each of the three scales will be summed and averaged, with higher scores indicating more favorable implementation outcomes. These data will provide added context to which factorial condition was perceived by both implementers and participants as most favorable. Collectively, these data will identify necessary implementation strategies, as well as facilitators and barriers to implementation, to guide future scale-up and scale-out activities throughout rural Appalachia.

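### The 12-item feasibility survey goes only to a random subset of participants and coaches, which costs precision for little saving

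*Protocol article*

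**What the plan says.** - **Role of the survey.** Study aim 2 states that "feasibility, appropriateness, and acceptability of the EBI will be assessed via a validated 12-item questionnaire". Table 1 lists the "Feasibility, acceptability, and appropriateness survey" under secondary outcomes.
- **Who completes it.** The Stakeholders part of Post-intervention says "we will ask stakeholders and selected peer health coaches to complete a psychometrically validated brief 12-item survey". The coaches are "a sample of randomly selected peer health coaches from each of the four factorial conditions". For participants, "we will also randomly select participants from each condition to complete the same survey and complete exit interviews". Stakeholders are not sub-sampled. No subset size is given for coaches or participants.
- **What is rated.** The same paragraph asks for ratings of the intervention as a whole and of each component of the factorial design.
- **How it is used.** Assessing implementation says "scores for each of the three scales will be summed and averaged", and then: "These data will provide added context to which factorial condition was perceived by both implementers and participants as most favorable".
- **Cell size.** In Sample size, "the decision was made to recruit 19 participants per condition for a total sample size of 76". Attrition is expected, but no rate is given.
- **Existing contact.** The Peer coaches and participants part of Post-intervention has the research coordinator collect HbA1c and the validated questionnaires from both groups at the end of the intervention. No sampling is mentioned there.

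**The concern.** Sampling is sensible for exit interviews, where each one takes staff time to conduct and code. It is harder to justify for a form that the protocol itself describes as brief, when the same people already complete questionnaires at the same time point. The sentence that selects participants ties survey and interview to one subset and gives no reason for limiting the survey.

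This is the instrument that aim 2 names for feasibility, acceptability and appropriateness, in a study described as a feasibility study. Its scores are to be read by condition, and a condition has at most 19 people. Any further cut widens an already wide interval.

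The sampling frame for coaches is also awkward. Participants are randomised, not coaches. Contact frequency follows the participant's assignment, and the same coaches serve all three waves. Nothing in the article confines a coach to one condition, so drawing coaches from each of the four conditions does not define clear strata.

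**Working it through.** **The plan's own figure.** The article gives no precision target for the survey. Its one design figure, a detectable Cohen's f of 0.33 at 80% power, concerns HbA1c. It reproduces: a 1-df contrast with N = 76 and four cells gives f = 0.326, and power at f = 0.33 is 81.0%. It says nothing about the survey.

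**Inputs for the survey**
- From the article: four conditions, 19 per condition, 76 in total.
- Assumed: SD of 0.7 points on a 1 to 5 scale.
- Assumed: subsets of 5, 8, 10 or 15 per condition. The 15 also serves as an illustration of a full survey after attrition.

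**Difference between two conditions.** Half-width = t(0.975, 2n − 2) × 0.7 × √(2/n).

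| n per condition | t | √(2/n) | 95% half-width (points) |
|---|---|---|---|
| 5 | 2.306 | 0.632 | 1.02 |
| 8 | 2.145 | 0.500 | 0.75 |
| 10 | 2.101 | 0.447 | 0.66 |
| 15 | 2.048 | 0.365 | 0.52 |
| 19 | 2.028 | 0.324 | 0.46 |

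**Difference between two levels of a factor.** Each level pools two conditions, so the group size is 2n.
- n = 5 (10 v 10): 2.101 × 0.7 × √(2/10) = 0.66 points.
- n = 8 (16 v 16): 2.042 × 0.7 × √(2/16) = 0.51 points.
- n = 19 (38 v 38): 1.993 × 0.7 × √(2/38) = 0.32 points.

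**In SD units, free of the assumed SD.** The difference between two conditions detectable at 80% power (two-sided 0.05) is 2.02 SD with 5 per condition, 1.51 with 8, 1.32 with 10 and 0.93 with 19. For a factor main effect it is 1.32, 1.02, 0.91 and 0.65 SD.

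**Reliability of the apparent favourite.** Suppose one condition is truly 0.5 SD better than three equal others. By simulation it has the highest mean in about 59% of trials with 5 per condition, 68% with 8, 72% with 10 and 86% with 19.

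**Number of coaches.** With equal waves (assumed) and three participants per coach, 76 / 3 = 25.3 participants per wave, and 25.3 / 3 = 8.4, so about 8 or 9 coaches. Sampling from so few saves almost nothing.

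**The case against.** **Other quantitative implementation data exist.** A reader might infer that this survey is the only quantitative feasibility measure. It is not. Encounter logs, a two-weekly participant survey of contact and content, importance and progress ratings at midpoint, and a PRISM-based survey are also planned. The 12-item form is the one that aim 2 names for these three constructs, and no more than that.

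**The use is soft.** A reader might infer that the scores will rank or select a condition. The text says only that they add context, read together with the interviews. No test or selection rule is attached to them, and the main comparison of conditions rests on HbA1c. This lowers the stakes, but scores read by condition still need usable precision.

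**The loss is not known.** A reader might infer that most of the information is discarded. That holds only if fewer than half are selected, and the fraction is not stated. Its absence is no finding, since the full protocol may give it. The point rests on the decision to sub-sample, which the article does fix.

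**Burden.** If the 12 items are answered for the whole intervention and for each of two components, that is 12 × 3 = 36 items; for the whole and four strategies, 12 × 5 = 60. Participants already face nine questionnaires besides HbA1c, and the Discussion concedes that data collection may be hard for older adults. Pairing survey and interview in the same people is a defensible mixed-methods choice. This is the strongest objection, and it makes the cost real but modest.

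**Limited gain.** Even with all 19, only a 0.93 SD difference between two conditions is detectable. That is true, and it argues against cutting the sample further and in favour of summarising by factor level.

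**Coaches.** The wording could mean coaches who have a participant in a given condition. The article does not exclude that reading, but a coach could then belong to several strata.

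**Conclusion.** The concern stands as a low-severity improvement to a secondary implementation outcome. The article fixes random sub-sampling of participants and coaches for the instrument that aim 2 names, and it does so where cells hold at most 19. The harm is lost precision, not bias: selection is random within condition. If 5 to 8 per condition were selected, the half-width for a two-condition difference would be about 1.6 to 2.2 times that of a full survey (0.75 / 0.46 and 1.02 / 0.46). These sizes rest on an assumed SD of 0.7, assumed subset sizes and no attrition; with a subset near 15 the loss would be small. The HbA1c analysis is unaffected.

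**What to change.** 1. Give the 12-item survey to every participant at the end-of-intervention questionnaire contact. Keep random selection for the exit interviews only.
2. Give it to every coach, and drop the sampling of coaches by condition.
3. Leave the component ratings as they are; they are already planned.
4. Summarise participant scores by factor level (selection method, contact frequency; up to 38 v 38) with 95% intervals, and show the four condition means as description.

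The cost is extra respondent time at an existing contact, with no added visit or staff. The burden exceeds 12 items if each component is rated separately, so the total item count should be settled before the form is added.

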### Study measurements and outcomes

Stakeholder’s data will be collected via semi-structured interviews pre-intervention, mid-intervention and post-intervention. Survey data will also be collected from stakeholders’ post-intervention. Peer coaches and peer participants will provide HbA1C levels via blood draw. Peer coaches will complete blood draws and questionnaire data at baseline and end of intervention across all three waves, whereas peer participants will complete blood draws and questionnaire data at baseline, end of intervention (6 months), 9 months and 12 months (see Table 1).

**Table 1 pone.0300196.t001:** Data collection measure instruments.

Measure	Method
**Primary Outcomes**	
Hemoglobin A1C	This will be collected via point-of-care assessment.
Medication Adherence	The Brooks Medication Adherence Scale will be used to assess medication adherence [41].
Quality of Life	The EuroQol-5D (EQ-5D) is a validated measure used to measure quality of life [42].
Diabetes-related emotional distress	The Problem Areas in Diabetes Survey (PAID) will assess diabetes-related emotional distress among adults [43].
Perceived Social Support	The Medical Outcomes Study (MOS) Social Support Survey will be used to assess perceived social support [44].
Problem-Solving Skills	The Diabetes Problem-Solving Inventory (DPSI) will assess how individuals living with diabetes cope with challenges of T2D-related self-care [45].
Depression	The Geriatric Depression Scale will be used to measure depression [46].
Self-Efficacy	The Diabetes Empowerment Scale measures diabetes-related psychosocial self-efficacy [47].
Diabetes Knowledge	The Diabetes Knowledge Questionnaire (DKQ) measures diabetes knowledge intervention [48].
Self-Care	The Diabetes Self-Management Questionnaire will assess self-care activity associated with glycemic control [49].
**Secondary Outcomes**	
Refine proposed operationalizations of RE-AIM dimensions	Qualitative interviews
Assess RE-AIM dimensions	Qualitative interviews
RE-AIM outcomes	Qualitative interviews
PRISM survey and interview guide	A PRISM-based survey [40] and an interview guide tested in previous applications of PRISM [34] across health systems to analyze PRISM contextual determinants
Feasibility, acceptability, and appropriateness survey	A psychometrically validated brief 12-item survey [40]
**Covariates**	
Personal characteristics (Age, Sex, Race/Ethnicity, Marital Status, County of Residence, Income)	All participants will provide answers to these personal characteristics
Physical Function	Lawton’s Instrumental Activities for Daily Living Scale will assess physical function [50].
Frailty	This will be assessed using a validated 4-item assessment that characterizes frailty by exhaustion, low physical activity, weakness, and low body mass index [51, 52].

#### Study measurements

The study measurements collected in the intervention include peer coach and participant interactions. Specifically, coach-peer interactions will be documented with the following: date, type of encounter (phone, in-person), duration, and topics discussed. Topics to be discussed include current and target clinical goals for A1c, cholesterol, blood pressure, self-care activities, managing stress, and SMART objectives. Self-report assessments will be used to track the effectiveness of the intervention.

#### Primary study outcomes

The outcomes of this study will be assessed against the objective of implementing a peer support intervention in Appalachia to improve the management of T2D in older adults.

(1) To use a 2x2 factorial design to determine which EBI components are associated with improved T2D-related outcomes in older adults living in Appalachia Kentucky by evaluating:

a. Peer coach selection (matched vs. self-selected) and frequency of contact (once per week vs. every 2 weeks) on
HbA1c, which will be collected via point-of-care assessment.T2D-related psychosocial factors (see Table 1).

#### Secondary study outcomes

(1) Evaluate the pragmatic implementability of the adapted EBI
To better understand implementability of the overall EBI, as well as each of the four strategies tested in the 2x2 factorial design, we will assess contextual factors that influence EBI adoption as well as implementation outcomes using the PRISM [53], a framework that incorporates RE-AIM dimensions. We will use a novel iterative approach to RE-AIM [54], wherein team members (both researchers and implementers) will collectively refine proposed operationalizations of RE-AIM dimensions and then, at project mid-point, identify RE-AIM dimensions needing added attention and set goals and strategies to improve progress on them, including potentially adapting or rejecting and replacing indicators to better capture necessary outcomes data. This iterative use of RE-AIM will ensure that any midcourse corrections are informed by pragmatic need and are documented accordingly.

## Data analyses

### Descriptive analysis

Descriptive data in the form of means (standard deviations) for interval-level variables and frequencies (percentages) for qualitative variables will be presented for the entire population and by trial arm. Prior to conducting and interpreting the main analyses, the distribution of all outcome variables will be examined to ensure the tenability of parametric assumptions.

### Analytic plan for aim 1

The repeated measures, factorial design will be analyzed using longitudinal linear mixed models. Linear mixed effects models are an extension of the general linear model and are suitable when the independence of observations assumption is violated, which occurs in this study when individuals are measured repeatedly over time. Additionally, these models have the benefit over a repeated measures ANOVA of utilizing all data from participants who were measured on some, but not necessarily all of the measurement occasions. The main outcome for this aim is HbA1c levels at the first post-intervention measurement occasion. Fixed effects of interest will include measurement occasion, peer support type, and contact frequency. Preliminary models will include all two-way interactions, and non-significant higher-order interactions will be removed to arrive at the most parsimonious model. The model will incorporate random effects to account for repeated measures on individuals using an autoregressive covariance matrix. Due to randomization, we do not anticipate any differences in covariates between groups; however, we will evaluate differences by main effects and adjust for them if necessary. Additional analyses related to Aim 1 will look at between-group differences in psychosocial factors over time.

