### Introductory session for peer coaches and participants

Peer participants and coaches will attend an introductory session together, during which the coaching process will be discussed, including time commitment, roles, responsibilities, benefits, and ground rules. At that time, peer participants who are randomized to self-select their coaches will have the opportunity to review peer coach profiles and rank their top three coaches to be matched. Once coaches and peers have been selected, the quads (coach with three peers) will have the opportunity to ask questions and make informed decisions about their ability to fully participate in the intervention. If face-to-face meetings are not possible for all members of the “quad,” phone or a form of video meeting will be attempted. At this time, the research coordinator will collect demographics, validated questionnaires, and baseline point-of-care clinical outcomes (HbA1c via fingerstick). This introductory meeting as well as the peer coach-peer participant meetings during the six months of intervention can be in-person in community settings or via Zoom, depending upon participants/coach preference.

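### The Aim 1 model, as stated, cannot estimate the selection-by-frequency interaction at 6 months, and for small effects its deletion rule will usually pool occasions into the factor effects

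*Protocol article*

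**What the plan says.** Under Analytic plan for aim 1 the protocol article fixes the time point: "The main outcome for this aim is HbA1c levels at the first post-intervention measurement occasion". It then lists the model terms: "Fixed effects of interest will include measurement occasion, peer support type, and contact frequency". On interactions it says: "Preliminary models will include all two-way interactions, and non-significant higher-order interactions will be removed to arrive at the most parsimonious model". On covariance: "The model will incorporate random effects to account for repeated measures on individuals using an autoregressive covariance matrix".

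Study measurements and outcomes sets four occasions: "peer participants will complete blood draws and questionnaire data at baseline, end of intervention (6 months), 9 months and 12 months". The introductory session, held before coaching starts, supplies the baseline value: "At this time, the research coordinator will collect demographics, validated questionnaires, and baseline point-of-care clinical outcomes (HbA1c via fingerstick".

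Sample size states what the pilot wants to learn: "This study is interested not only in main effects, but also an interaction between peer support intervention and contact frequency". The same section gives preliminary effect sizes for each factor, to power a larger trial, as the purpose of the study.

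The article names no three-way term, protects no term from removal, specifies no 6-month contrast, and does not say whether baseline HbA1c enters as a response or as a covariate.

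**The concern.** Write T for occasion, A for coach selection and B for contact frequency. The stated starting model has T×A, T×B and A×B.

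- **Interaction.** Without T×A×B, the A×B coefficient is one number for all occasions. It cannot be the interaction at 6 months unless the interaction is the same at every modelled occasion. If baseline is one of them, that cannot hold for a real interaction, because nothing has been delivered at baseline.
- **Factor effects.** T×A and T×B are what allow a factor effect at 6 months to differ from the effect at baseline. If they are removed for non-significance, the remaining A or B coefficient is a pooled value over occasions, and the final model holds no 6-month effect.

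At stake are the effect sizes that the pilot exists to provide. The larger trial would be sized on pooled values taken from a model chosen by p-value, with standard errors that ignore the choice.

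**Working it through.** **Inputs from the article.** N = 76, 19 per condition ("the decision was made to recruit 19 participants per condition for a total sample size of 76"), hence 38 v 38 for each factor. Four occasions. Two-sided α = 0.05. Detectable effect f = 0.33 at 80% power; small effect given as an example, f = 0.1. For a two-level factor d = 2f.

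**Assumptions (not in the article).** AR(1) correlation r = 0.5, 0.7 or 0.8 between successive occasions, treated as equally spaced; compound symmetry 0.5 and 0.7 as a variant. Effect profile over 0, 6, 9 and 12 months, relative to 6 months: sustained (0, 1, 1, 1) or waning (0, 1, 0.5, 0.25). Unit SD, no dropout.

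**1. The article's own figure.** Noncentral F with 1 and 72 df and noncentrality N·f². 80% power is reached at f = 0.326, and power at f = 0.33 is 81.0%, so the stated 0.33 reproduces as a 1-df effect without attrition. (A 3-df omnibus test would give 0.389.) At f = 0.1 the power is 13.8%.

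**2. Weights in a pooled coefficient, baseline as an outcome row.** A term held constant over occasions is estimated with generalised-least-squares weights proportional to V⁻¹1. For AR(1) with four occasions these are (1, 1−r, 1−r, 1)/(4−2r).

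| r | baseline | 6 mo | 9 mo | 12 mo | sustained | waning |
|---|---|---|---|---|---|---|
| 0.5 | 0.333 | 0.167 | 0.167 | 0.333 | 67% | 33% |
| 0.7 | 0.385 | 0.115 | 0.115 | 0.385 | 62% | 27% |
| 0.8 | 0.417 | 0.083 | 0.083 | 0.417 | 58% | 23% |

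The last two columns are the pooled coefficient as a share of the 6-month effect. Example, r = 0.5, waning: 0.167×1 + 0.167×0.5 + 0.333×0.25 = 0.33. Under compound symmetry each weight is 0.25, giving 75% and 44%.

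These shares apply to A×B always, because T×A×B is absent. They apply to A or B once its occasion term is dropped.

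**3. How often T×A (or T×B) is dropped.** 3-df F test at 0.05 on the occasion-specific factor differences, whose covariance is V·4/76. Range over all correlations and profiles above:

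| f | dropped |
|---|---|
| 0.1 | 79–90% |
| 0.2 | 29–71% |
| 0.33 | 1–29% |

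**4. What the whole procedure delivers** (200,000 simulated contrasts per setting; 6-month estimate if T×A is kept, pooled estimate if not). The mean is 48–83% of the true 6-month factor effect at f = 0.1 and 88–100% at f = 0.33. At f = 0.1 the true d is 0.20 SD, so the shortfall is (1−0.83)×0.20 to (1−0.48)×0.20, about 0.03–0.10 SD. The standard error of a 6-month factor contrast is √(4/76) = 0.229 SD, so this is about 0.15–0.45 standard errors. Coverage of nominal 95% intervals is lowest at 71% (waning, AR(1) 0.5, f = 0.2).

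**5. Baseline as a covariate.** Pooling is then over 6, 9 and 12 months. A sustained effect gives 100% of the 6-month value. For the waning profile, equal weights (compound symmetry) give (1 + 0.5 + 0.25)/3 = 58%. Under AR(1), adjusted for baseline, the weights are proportional to (1−r+r², (1−r)², 1−r). At r = 0.5 these are 0.50, 0.17 and 0.33, giving 67%; at r = 0.8 they are 0.78, 0.04 and 0.19, giving 84%.

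**6. With all terms kept.** Both factor contrasts and the interaction contrast at 6 months are recovered at 100% of their true values. Power for a factor contrast is about 81% at f = 0.33, in line with the article's design figure, and stays about 14% at f = 0.1.

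**The case against.** Four points deserve weight.

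- **The wording is ambiguous.** Higher-order may mean the two-way terms, which are higher than main effects, or terms above two-way. On the second reading the occasion × factor terms stay and the 6-month factor effects survive. The plain reading is that the terms to be removed are those just listed, and only two-way terms are listed. If a three-way term was meant, the same rule would delete it when non-significant. The ambiguity weakens the factor-effect part, not the interaction part.
- **Baseline may be a covariate.** The article does not say. Step 5 then applies, and a sustained effect suffers no bias. This stands, and the figures in step 2 depend on it.
- **This is a pilot.** It makes no confirmatory claim, and the shortfall in a factor effect at f = 0.1 is under half a standard error. That is fair on size. But effect sizes are the stated product, and this error is systematic.
- **Exact contrasts are commonly left to an analysis plan.** True, and their absence alone would be no finding. The issue is that the model and removal rule that are stated conflict with the outcome stated in the same section.

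A reader might infer that the plan usually averages baseline into the factor effects. The documents do not support that without a condition: it holds at f = 0.1, is mixed at f = 0.2, and fails at the detectable f = 0.33. A reader might also infer that estimates always shrink. When the occasion term survives the test at f = 0.1, the 6-month estimate is too high (about 0.25–0.38 SD against a true 0.20).

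**Conclusion.** The concern holds in a conditional form. By algebra, and whatever the effect size, the model as stated gives no 6-month selection-by-frequency interaction, although the article names that interaction as of interest and fixes the outcome at 6 months. How far the pooled value misses depends on things that the article does not give. With baseline as an outcome row and AR(1) 0.5–0.8, it is 58–67% of the 6-month interaction if sustained and 23–33% if waning. With baseline as a covariate, it is biased only if the effect changes over time.

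The same pooling reaches a factor effect only if the removal rule covers the occasion × factor terms and the term is dropped. That is the usual result for effects near f = 0.1 and an uncommon one near f = 0.33. All percentages rest on assumed correlations and effect profiles.

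**What to change.** Replace the interaction and removal sentence with one pre-specified model: categorical occasion × selection × frequency, all terms kept whatever their p-values. State the role of baseline: either an outcome row with means constrained equal across the four arms, or a covariate. Report three contrasts at 6 months with 95% CIs as the primary results (selection, frequency and their interaction). Report the same contrasts at 9 and 12 months as secondary, from the same model.

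The cost is wording, a few more parameters and some precision. A 6-month contrast that makes no use of baseline has a standard error of 0.229 SD, against 0.162–0.199 SD for one pooled over all four occasions under AR(1) 0.5–0.8. Constraining baseline means recovers part or all of this, since the 6-month standard error becomes 0.229×√(1−r²): 0.199 at r = 0.5 and 0.138 at r = 0.8. No new data or participants are needed. The fix does not raise the pilot's low power for small effects; it makes the reported estimates refer to the time point that the article names.
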